**Figure 1 F1:**
[figure not shown]
**Flow diagram of the study participants**.

### Randomisation and blinding

The participant randomisation assignment will follow an allocation concealment process, that is, the researcher in charge of randomly assigning participants will not know in advance which treatment the next person would receive and will not participate in assessment. Assessment staff will be blinded to participant randomisation assignment. Participants will be explicitly informed on the group to which they will be assigned as well as on the study hypotheses and will be reminded not to discuss their randomisation assignments with assessment staff. It will not be possible to conceal the group assignment from the staff involved in the training.

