## Presentation of the hypothesis

We hypothesised that: (i) a 24-weeks exercise intervention training (either water- or land-based) would be effective for reducing the impact of fibromyalgia (primary outcome), and improving tenderness and pain-related measures, body composition, functional capacity, physical activity and sedentary behaviour, fatigue, sleep quality, health-related quality of life and cognitive function (secondary outcomes) in women with fibromyalgia; (ii) a 24-weeks land-based aerobic-strength intervention training could be as effective as a water-based intervention; and (iii) the exercise training-induced gains would be partially retained in the intervention groups after the detraining period such that their physical status will still be better than that of the control group at this time point.

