### Sample size

The required sample size was determined for the primary outcome variable, i.e. overall score of Fibromyalgia Impact Questionnaire (FIQ) [30]. According to previous research [31], a clinically relevant change is a 15-20% reduction in the total FIQ score (which equals to a ~10-15 points reduction). Assuming an unilateral alternative (i.e. the intervention reduces impact of fibromyalgia), we can detect differences of at least 15% with a power of 95% and α of 0.05 with two groups (intervention and usual care group) of 45 participants, with a mean in the FIQ of ~70 and a standard deviation of ~20 points. Assuming a maximum lost of follow-up of 30%, we will recruit a total of 60 women with fibromyalgia for each group. Since we will develop two types of interventions (land and water-based), we will recruit a total of 180 women with fibromyalgia (i.e., two intervention groups and one usual care group of 60 persons each). Figure 1 shows the flow diagram of the study participants

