### Primary outcomes measures

*Fibromyalgia Impact Questionnaire *(FIQ) is a self-administered questionnaire, comprising 10 subscales of disabilities and symptoms (physical function, work missed day, job ability, feel good, pain, fatigue, sleep, stiffness, anxiety and depression) and has been validated for Spanish fibromyalgia patients [30]. The total scores range from 0 to 100, with a higher score indicating greater effect of the condition on the person's life.

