### Assessment

The outcomes will be assessed just before the intervention (baseline), after 24 weeks of exercise interventions (post-intervention) and after 12 weeks of training cessation (detraining). The assessments of the primary and secondary outcomes will be performed on two separate days in order to prevent fatigue in the patients. The patients will complete some questionnaires at home between day 1 and 2. The study assessment schedule is shown in Table 2.

**Table 2 T2:** Study Assessment Schedule

Assessment	Screening	Baseline	Intervention	Post-intervention (24 weeks)	Detraining (12 weeks)
- Informed Consent	X				

*Day 1 testing*					
- Sociodemographic data	X			X	X
- Mini Mental State Examination	X				
- Physical Activity Readiness Questionnaire-PAR-Q	X				
- Beck Depression Inventory-II	X			X	X
- Tender points	X			X	X
- Visual analogic scale for pain		X	X	X	X

*Questionnaires to complete at home between day 1 and 2*					
- Fibromyalgia Impact Questionnaire		X		X	X
- Short-Form Health Survey 36		X		X	X
- State Trait Anxiety Inventory-I		X		X	X
- Trait Meta-Mood Scale		X		X	X
- Positive and Negative Affectivity Schedule		X		X	X
- Satisfaction With Life Scale		X		X	X
- Life Orientation Test Revised		X		X	X
- Pittsburgh Sleep Quality Index		X		X	X
- Multidimensional Fatigue Inventory		X		X	X
- ALPHA Environmental questionnaire		X		X	X
- Sedentary Behavior Questionnaire		X		X	X
- Physical activity at homework or workplace instrument		X		X	X
- Leisure time physical activity instrument		X		X	X
- International Fitness Scale		X		X	X
- Chronic Pain Self-Efficacy Scale		X		X	X
- Pain Catastrophizing Scale		X		X	X

*Day 2 testing*					
- Paced Auditory Serial Addition Task		X		X	X
- Rey Auditory Verbal Learning Test		X		X	X
- Body composition		X		X	X
- Chair sit and reach test		X		X	X
- Back scratch test		X		X	X
- Arm curl test		X		X	X
- 30-s chair stand test		X		X	X
- 8 ft up and go test		X		X	X
- Handgrip strength		X		X	X
- 6-min walk test		X		X	X
- Accelerometry (1 week)		X		X	X

- Patient Global Impression of Improvement scale				X	

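### Participants are told the study hypotheses as well as their group, an avoidable risk of expectation bias in a self-completed primary outcome

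*Protocol article*

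**What the plan says.** Randomisation and blinding describes two groups of people differently. For staff: "Assessment staff will be blinded to participant randomisation assignment". For participants: "Participants will be explicitly informed on the group to which they will be assigned as well as on the study hypotheses". They are also asked not to reveal their group to the assessors. The article gives no reason for disclosing the hypotheses.

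Presentation of the hypothesis lists three. The first is that "a 24-weeks exercise intervention training (either water- or land-based) would be effective for reducing the impact of fibromyalgia (primary outcome"). The second is that "a 24-weeks land-based aerobic-strength intervention training could be as effective as a water-based intervention". The third is that part of the gain survives the 12 weeks without training, so that the trained groups' physical status remains better than that of controls.

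The sample size is set on the total FIQ score. Under Primary outcomes measures, the FIQ "is a self-administered questionnaire, comprising 10 subscales of disabilities and symptoms", among them pain, fatigue, sleep, anxiety and depression. In Assessment, Table 2 places it under "Questionnaires to complete at home between day 1 and 2" at baseline, at 24 weeks and after detraining.

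Under Usual care group, controls receive general advice from the exercise monitor on the benefits of physical activity, together with pamphlets.

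**The concern.** When a patient rates her own symptoms, she is the outcome assessor. Here she knows her group and is also told what result the investigators expect. The natural reading of the first and third hypotheses is that exercise should do better than usual care. A woman in an exercise group may then rate herself somewhat better, and a control somewhat worse, than she would have done without that information.

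Such a shift would act in the direction of the primary claim and would look the same as a treatment effect in the data. Randomisation does not prevent it, because it arises after allocation. Staff blinding does not prevent it either, because staff do not rate the FIQ. At stake is whether a modest FIQ difference between exercise and usual care can be read as an effect of exercise.

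**Working it through.** **Step 1: who could be affected, and when.**

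| Element | What the article fixes | Consequence |
|---|---|---|
| Knowledge of group | Participants told (Randomisation and blinding) | Unavoidable in an exercise trial |
| Knowledge of hypotheses | Participants told (same sentence) | Avoidable; no reason given |
| Direction against control | Exercise reduces impact; trained women better off after detraining (Presentation of the hypothesis) | Possible bias favours exercise |
| Land versus water | Similar effect (same section) | No direction implied |
| Rater of the FIQ | The patient, at home (Primary outcomes measures; Table 2) | Staff blinding does not reach it |
| Time of allocation | After baseline (Testing the hypothesis) | Knowledge of the group can affect only the 24-week and detraining FIQ |

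**Step 2: can the analysis repair it?** Statistical analysis plans ANCOVA with age and baseline as covariates, adjustment for multiple comparisons, intention-to-treat, multiple imputation with sensitivity analysis for missing responses, and a look at regression to the mean. None of these separates a difference in reporting after baseline from a difference in symptoms.

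**Step 3: the plan's own figures.** Sample size gives 45 per group, SD about 20, mean about 70, one-sided α 0.05 and power 95%. With n = 2(1.645 + 1.645)² × 20² / d²:
- d = 15% of 70 = 10.5 points gives 78.5, so 79 per group.
- d = 20% of 70 = 14 points gives 44.2, so 45 per group.

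The stated 45 therefore reproduces at 20% and not at the stated 15%. That is a separate matter. Only n = 45 and SD = 20 are used below.

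**Step 4: illustration of what a reporting shift would do.** The documents give no size for it. The range of 2 to 6 points (0.1 to 0.3 SD) is an assumption. Against the 10.5-point difference it is 2/10.5 = 19% to 6/10.5 = 57%.

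Standard error of the difference: 20 × √(2/45) = 4.216 points. With no true effect and a shift b towards exercise, z = b/4.216. Then
- one-sided error = 1 − Φ(1.645 − z);
- two-sided error = 1 − Φ(1.960 − z) + Φ(−1.960 − z).

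| Shift b (points) | z | One-sided 5% becomes | Two-sided 5% becomes |
|---|---|---|---|
| 0 | 0 | 5% | 5% |
| 2 | 0.474 | 12% | 8% |
| 4 | 0.949 | 24% | 16% |
| 6 | 1.423 | 41% | 30% |

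This is a simple two-group comparison. Covariate adjustment and imputation would change the standard error and could move these figures either way.

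**The case against.** The strongest reply is that expectation cannot be removed from this trial. Women know whether they are exercising, and many will expect exercise to help whatever they are told. Only the increment from stating the hypotheses is avoidable, and nothing in the documents measures it. This stands. The table in the working cannot be attributed to the disclosure, because it covers any differential shift, including the part due to unavoidable unblinding. The one-sided column also rests on the sidedness used for the sample size; Statistical analysis fixes none for the tests.

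A reader might infer that controls are told to expect no benefit. The article does not say so. The hypotheses place exercise ahead of control but do not say that controls will fail to improve, and controls are themselves advised that activity is beneficial. Nor are the words actually used with participants shown, so a balanced presentation cannot be excluded.

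A reader might also infer that completing the FIQ at home is itself a source of bias, or that the land versus water comparison is tilted. Neither is supported. Home completion matters here only because it confirms that a blinded assessor has no part in the rating, and the hypothesis for the two exercise forms is similarity.

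The trial also has staff-assessed and device-based outcomes, such as the functional tests, bioimpedance and accelerometry. They can corroborate a finding but do not protect the FIQ.

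Two defences do not stand. Informed consent can describe the purpose, the groups and the uncertainty without predicting the result. And this is not detail lost in a condensed article, since the article states the disclosure outright.

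**Conclusion.** The point holds as an avoidable risk of bias in the primary outcome, not as a demonstrated bias. The disclosure, the unblinded participant and the self-completed FIQ are all stated in the article. The direction of the risk is towards exercise over usual care, and it applies to post-baseline scores only.

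Its size is unknown. The 12% to 41% range (24% one-sided and about 16% two-sided at 4 points) depends on an assumed shift, SD 20, 45 per group and no true effect. It shows how sensitive the comparison is to a shift of a few points; it does not estimate the effect of telling women the hypotheses. Reading it as the trial's actual false-positive rate would go beyond the documents. The change is worth making because it is cheap and because the analysis cannot undo the problem afterwards.

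**What to change.** In Randomisation and blinding, delete the clause that has participants informed of the hypotheses; keep the statement that they are told their group. Give all women the same neutral consent information: describe the three groups and say that it is not known which is best, without the trial's expected result.

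Leave the general physical activity advice and pamphlets of the usual care group as they are. They form the control condition, and altering them would change the comparison.

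The cost is rewording of this passage and of the participant information. Because the ethics committee approved the informed consent procedure (Testing the hypothesis), the changed information would probably need its re-approval. The sample size and assessments are unaffected.

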### Statistical analysis

For between groups comparisons at baseline (usual care vs water-based intervention vs land-based intervention), we will analyse continuous variables with one-way analysis of variance or the non-parametric method of Kruskall-Wallis, and Chi-square tests (or exact techniques if needed). We will use analysis of covariance (ANCOVA) to assess the training effects on the primary and secondary study outcomes (or the rank-transform ANCOVA). Age and baseline level of each outcome variable will be entered as covariates. For each outcome variable we will report the effect size and the level of significance corresponding to the main group (between-subjects), time (within-subjects) and interaction (group × time) effects.

We will adjust multiple comparisons for mass significance [32]. We will also examine the differences between drop-outs and participants who remain in the study. We will analyse the data according to the intention-to-treat principle [33]. We will handle missing data due to drop-outs or non-compliance using multiple imputation methods. To fully appreciate the potential influence of missing responses, we will perform sensitivity analysis. In all analyses, we will study the effect of the regression towards the mean.

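### Rank-transform ANCOVA, allowed for every outcome, does not reliably hold the level of the promised group × time test in skewed outcomes, and a ranked FIQ result could not be read in points

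*Protocol article*

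**What the plan says.** Under Statistical analysis the protocol article states: "We will use analysis of covariance (ANCOVA) to assess the training effects on the primary and secondary study outcomes (or the rank-transform ANCOVA". The alternative therefore covers the FIQ as well as every secondary outcome. The same paragraph adds that "Age and baseline level of each outcome variable will be entered as covariates", and that an effect size and significance level will be given for each outcome for the "main group (between-subjects), time (within-subjects) and interaction (group × time) effects".

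Three other sections bear on this:

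- **Assessment:** after baseline, outcomes are measured "after 24 weeks of exercise interventions (post-intervention) and after 12 weeks of training cessation (detraining".
- **Presentation of the hypothesis, item (iii):** "the exercise training-induced gains would be partially retained in the intervention groups after the detraining period", with the exercise groups still better off than control at that point.
- **Sample size:** "a clinically relevant change is a 15-20% reduction in the total FIQ score", put at roughly 10-15 points.

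**The concern.** The plan attaches a rank method to an interaction test. Ranking is non-linear: a shift of a given number of points moves an observation through many ranks where scores are dense and through few where they are sparse. Profiles that are parallel in points can therefore diverge in ranks. The group × time test asks whether the exercise-control difference changes between the end of training and detraining. A false positive there would be read as training gains lost, or further gained, after training stops. Skewed data are the natural occasion for the fallback and also the setting in which ranks distort most.

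The second matter is scale. Relevance and sample size are set in FIQ points or percent of the FIQ total. A rank-transform estimate is a difference in mean ranks, so it cannot show whether exercise reached that threshold.

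**Working it through.** **Inputs from the protocol.** Mean FIQ about 70, SD about 20, 60 women per arm (45 before the dropout allowance), three arms, age and baseline as covariates. The relevant change reproduces approximately: 0.15 × 70 = 10.5 and 0.20 × 70 = 14 points, against the stated 10-15. In SD units these are 10.5/20 = 0.525 and 14/20 = 0.70.

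**Assumptions not in the protocol.** Within-person correlation 0.6 (also 0.8), the error shapes, the size of any time shift common to all arms, and the 20-point effects (20/20 = 1 SD) used as a stress case.

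**Which times enter the test.** Baseline is a covariate, so I read the levels of time as post-intervention (t = 1) and detraining (t = 2).

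**Why pooled ranks can fail.** Let Y be the outcome of a woman in group g, with group effect γ_g at both times, common shift τ from t = 1 to t = 2, and no interaction in points. With two times, the interaction test compares the mean of (time 2 − time 1) across arms.

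- In points, that mean is τ in every arm, so the null is true.
- In pooled ranks over 2N values, rank ≈ 2N·F(Y), where F is the pooled distribution. The mean change in arm g is about 2N·E[F(Y_g + τ) − F(Y_g)], which depends on where arm g lies.
- If τ = 0 it is zero in every arm. If all γ_g are equal it is the same in every arm. The level is at risk only when a group effect and a common shift coexist.

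**Size under log-normal errors.** Log-SD 0.8, SD 20, 60 per arm, correlation 0.6, no interaction in points, nominal 5%. The ranges are over repeated simulations:

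| Group effect / common time shift (points) | Pooled-rank group × time rejection |
|---|---|
| 10.5 / 10.5 | 7.1-7.8% |
| 14 / 10.5 | 10.8-12.1% |
| 20 / 20 | 19.0-21.2% |

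**Size under other conditions.** A further set of simulations used 45 or 60 per arm and time shifts of −10 to 20 points:

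| Setting | Pooled-rank rejection |
|---|---|
| Normal, 10.5-14 points | 4.2-6.4% |
| Normal clipped to 0-100, 10.5-14 points | 4.0-5.3% |
| Exponential, up to 14 points | 4.4-6.5% |
| Log-normal, 14 points with a shift, correlation 0.6 | 7.6-12.3% |
| Log-normal, 14 points with a shift, correlation 0.8 | 17.5% |
| Log-normal, 20 points, shifts 10-20 | 17.4-34.4% |
| Log-normal, 10.5 points, no common shift | 5.0% |

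Raw-scale ANCOVA gave 4.0-6.2% throughout. Near 5%, the Monte Carlo standard error is √(0.05 × 0.95 / runs): 0.4 percentage points at 3,000 runs and 0.6 at 1,500.

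**Ranking within each time.** This held the level (3.6-6.6%). But each time point then has mean rank (N + 1)/2. With all 180 women that is 181/2 = 90.5 at both times, so the overall time effect is zero by construction. Of these two ranking schemes, the one that keeps the interaction level cannot supply the time effect that the plan promises.

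**Ranks at one time point.** The rank-transform test of group at a single time held its level (4.5-5.1%).

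**The case against.** The strongest case against has four parts.

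1. **The ranking scheme is not stated.** The article does not say that ranks are pooled, and within-time ranks keep the level. That is correct, and it rules out calling the fallback invalid outright. It does not rescue the text, because within-time ranks cannot deliver the promised time effect.

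2. **The settings are severe.** They need marked skew plus a sizeable shift in all arms, controls included, between the end of training and detraining. The article predicts no such shift. In the log-normal setting, no shift gave 4.8% and a 5-point shift 6.3%. This stands and limits the point.

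3. **Partial retention is itself an interaction.** The simulated null is therefore not what the plan expects. True, but full retention is the null that this test must be able to leave standing, and it implies equal group effects at both times.

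4. **Raw FIQ means might be shown beside rank p-values.** Nothing excludes that. The loss of the point scale arises only if FIQ is ranked and no point difference is given.

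A reader might also infer that leaving the choice between two analyses open inflates the primary type I error. The documents do not support this. The rule for switching is a detail that an article may leave to the SAP. A switch driven by a normality test gave 4.7-5.1%. Only taking the smaller of the two p-values gave 6.0-7.7%, and the plan nowhere proposes that.

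**Conclusion.** The point holds in limited form. As written, the plan commits to a group × time result for each outcome, including any analysed on ranks. With ranks pooled over post-intervention and detraining, that test has no guaranteed level when a group effect and a common time shift coexist. Under log-normal errors with correlation 0.6, the nominal 5% becomes about 7% at 10.5-point effects and about 21% at 20-point effects. These figures rest on the assumed skew, correlation and shift.

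The stronger reading, that rank-transform ANCOVA is never a valid test here, is not supported. The test keeps its level with no group effect or no common shift. It also does so if baseline were a level of time: randomisation then makes no interaction equivalent to no treatment effect, and simulation gave 4.1-5.7%. For near-normal or bounded FIQ scores at the planned effects the distortion is negligible, and group comparisons at one time are unharmed. The practical exposure is in skewed secondary outcomes. For FIQ the issue is interpretability: a ranked estimate cannot be set against the plan's own relevant change.

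**What to change.** Replace the open alternative with three statements:

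1. FIQ total is analysed by ANCOVA on its point scale and reported as adjusted differences in points with robust or bootstrap confidence intervals.
2. For skewed secondary outcomes, rank-transform ANCOVA is used only for between-group comparisons at a single time point, post-intervention or detraining.
3. Group × time is tested on the original scale with robust or bootstrap inference, not on ranks.

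A log transformation is no substitute in item 3 if the question is about points. It is also non-linear, and in the log-normal settings with a common shift of 10.5 points or more its interaction test rejected 54-100% of the time with no interaction in points.

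The cost is wording only: no new data and no change in sample size. There would be no rank-based interaction p-value, and intervals for heavily skewed outcomes may be wider.

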### Interventions

The interventions will be performed in waves so that each wave will have between 10 and 12 participants in the intervention groups, and 10-12 in the usual care group. The land-based and water-based intervention groups will train 3 days/week (60 min per session) for a 24-week period. The intervention will involve exercises for improving cardiovascular endurance, muscle strength, and joint range of motion. The exercise interventions will meet the minimum training standards of the American College of Sports Medicine [34]. The exercise sessions will be carefully supervised by an exercise monitor.

The exercises will involve all major muscle groups. During the first weeks, the main part of the sessions will focus on teaching the patients how to perform the exercises. Each session will include 10 min of warm-up with slow walks and mobility exercises, followed by 35-40 min of aerobic exercises, developed progressively at intensity sufficient to achieve 50% (at the beginning of the intervention) and ~80% (the last month of the intervention) of predicted maximum heart rate (209-0.73 × age), and resistance strength training. Finally, each session will end with 10 min of cooling down with low-intensity, flexibility and relaxation exercises.

Heart rate will be assessed with a heart rate monitor (Polar Electro OY, Finland) in order to control the intensity of the sessions. One third of the patients in the intervention group will wear heart rate monitors in 1/3 of the sessions, both randomly selected. We will also monitor the rate of perceived exertion (RPE) using the Borg's conventional (6-20 point) scale [35]. Intensity (expressed as RPE) will range from 12 to 14. These RPE values correspond to a subjective perceived exertion of "light" and "somewhat hard" respectively. Overexertion will be checked by the "Talk test", that is, during exercise sessions participants will be able to maintain a conversation without getting breathlessness [36].

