#### Land-based intervention

The land-based exercise intervention group will train in the exercise training facilities of the local association of fibromyalgia, or in the closer exercise centre. Cardiovascular exercises will incorporate walking at different speeds and continuous and rhythmic activities that affects large muscle groups and aerobic dance. Resistance strength training will include 1-3 set of 8-12 repetitions. The strengthening exercises will include biceps curls, arm extensions, arm side lifts, shoulder elevations, lateral leg elevations, stands up from seated position, lunge, sideways lunge and step-up/step-down. The load will be gradually increased as the strength of each person improves. We will use body weight at the start of the program and barbells (0.5-2 kg per exercise). Flexibility will be developed by static stretching at the end of the warm-up and cool-down periods.

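### Exercise is delivered in supervised groups but the stated ANCOVA treats all women as independent, so its standard errors are too small if outcomes are correlated within a training class

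*Protocol article*

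**What the plan says.** The protocol article, Interventions section, describes delivery in groups: "The interventions will be performed in waves so that each wave will have between 10 and 12 participants in the intervention groups", with 10-12 usual care women in the same wave. Both exercise programmes run three times a week for 24 weeks. On supervision the section says: "The exercise sessions will be carefully supervised by an exercise monitor". Under Land-based intervention, the land group "will train in the exercise training facilities of the local association of fibromyalgia, or in the closer exercise centre"; the water group trains in a pool. Usual care women receive advice and pamphlets and attend no sessions (Usual care group (control)). Women are recruited through several local associations (Participants and selection criteria).

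The Statistical analysis section chooses ANCOVA, or its rank-transform form, for primary and secondary outcomes. On covariates it says: "Age and baseline level of each outcome variable will be entered as covariates". It mentions no term for wave, class, exercise monitor or association, and no random effect or cluster-robust variance. The Sample size section plans 45 evaluable and 60 recruited women per group, 180 in all, with no design effect.

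**The concern.** Women who train together for 24 weeks share classmates, a venue and a supervised programme, so their outcomes may resemble each other more than those of women in different classes. Usual care has no such structure. The design is therefore partially nested: clustered in two arms and unclustered in the third. The ANCOVA as written estimates its error as if every woman were independent.

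At stake are the significance level and interval width for each exercise arm against usual care, and more so for land against water, where both arms are clustered. The second comparison is one of the stated hypotheses (Presentation of the hypothesis), under which land could be as effective as water. Intervals that are too narrow could lend that conclusion support it has not earned.

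Wave is a separate matter. If exercise and usual care women run concurrently within a wave, a wave effect is common to them and cancels from their difference, but it stays in the error term when wave is omitted.

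**Working it through.** **The plan's own sample size.** The Sample size section states: "we can detect differences of at least 15% with a power of 95% and α of 0.05 with two groups" of 45, one-sided, "with a mean in the FIQ of ~70 and a standard deviation of ~20 points". With n per group = 2 × [SD × (z₀.₉₅ + z₀.₉₅) / difference]²:
- 15% of 70 = 10.5 points: 2 × (20 × 3.290 / 10.5)² = 78.5, so 79 per group. With 45 per group the power is 80.1%.
- 20% of 70 = 14 points: 2 × (20 × 3.290 / 14)² = 44.2, so 45 per group. The power is 95.3%.

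The stated 45 thus fits 14 points, not 10.5. That is a separate matter; both differences are carried forward below. Neither calculation contains a clustering term.

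**Number and size of classes.** 60/12 = 5 and 60/10 = 6, so 5-6 classes per exercise arm if 10-12 means per arm per wave. Evaluable women per class: 45/5 = 9, or 45/6 = 7.5. The main calculation uses m = 9.

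**Formulas.** The ICC is assumed; the document gives none.
- Design effect in an exercise arm: DE = 1 + (m − 1) × ICC.
- True SE / model SE: √[(1 + DE)/2] for one exercise arm against usual care; √DE for land against water.
- True two-sided level: 2 × P(Z > 1.96 / ratio).
- Power against usual care: Φ(difference / [20 × √((1 + DE)/45)] − 1.645).

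| ICC (assumed) | DE | SE ratio vs usual care | Two-sided level | SE ratio, land vs water | Two-sided level | Power at 14 points | Power at 10.5 points |
|---|---|---|---|---|---|---|---|
| 0 | 1.00 | 1.00 | 5.0% | 1.00 | 5.0% | 95.3% | 80.1% |
| 0.01 | 1.08 | 1.02 | 5.5% | 1.04 | 5.9% | 94.6% | 78.7% |
| 0.02 | 1.16 | 1.04 | 5.9% | 1.08 | 6.9% | 93.9% | 77.4% |
| 0.05 | 1.40 | 1.10 | 7.4% | 1.18 | 9.8% | 91.7% | 73.5% |
| 0.10 | 1.80 | 1.18 | 9.8% | 1.34 | 14.4% | 87.7% | 67.7% |

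On the one-sided basis used for planning, the level against usual care is 5.3 / 5.7 / 6.7 / 8.2% for ICC 0.01 / 0.02 / 0.05 / 0.10.

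**Sensitivity to class size, at ICC 0.05.** With 7.5 to 12 women per class, the two-sided level runs from 6.9% to 8.3% against usual care and from 8.9% to 11.5% for land against water.

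**Simulation of the stated ANCOVA.** One exercise arm against usual care, 45 per arm, 5 classes of 9, assumed baseline-outcome correlation 0.5, 6,000 runs. The simulation error near 5% is √(0.05 × 0.95/6000) = 0.3 percentage points.
- No clustering: 4.4% two-sided.
- Class ICC 0.05: 7.1%, SE ratio 1.10.
- Class ICC 0.10: 10.2%, SE ratio 1.20.
- Shared wave effect only, ICC 0.05: 5.0% (SE ratio 0.99); ICC 0.10: 4.0% (SE ratio 0.96).
- Class ICC 0.05 with wave ICC 0.05: 7.2%.

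Class effects make the SE too small. A shared wave effect makes it slightly too large, visibly so only at the higher ICC.

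**The wave sentence against the totals.** 60 usual care women at 10-12 per wave give 5-6 waves. If 10-12 were the land and water total per wave, exercise to usual care would be 1:1, against 120:60 in the Sample size section. Read as 10-12 per arm, the sentence fits 60/60/60.

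**The case against.** The strongest reply is that this is a condensed article. It lists age and baseline as covariates without saying they are the only terms, and a full analysis plan could add a cluster term. That possibility stands. But the article does more than stay silent: it selects the model and lists its covariates, and that model, followed as written, does not match the delivery it describes.

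A second reply is that the class ICC may be small. Make-up sessions are allowed, attention and load are individualised, intensity is controlled by heart rate and perceived exertion, and one monitor may serve several classes. The article does not say that each arm within a wave is one fixed class with its own monitor. This stands as a limit on size: at ICC 0.01-0.02 the SE against usual care is off by only about 2-4%.

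Three stronger readings are tempting and not supported:
- A reader might infer that the standard errors are wrong outright. Without an ICC, the error is conditional, and it is zero if the ICC is zero.
- A reader might infer that ignoring wave also inflates the error rate. The simulation shows the opposite direction for a wave effect shared by the arms.
- A reader might infer that land and water ran in different waves, so that their comparison is confounded with wave. Nothing says so. Allocation is described as three-way (Testing the hypothesis), and 60/60/60 fits 10-12 per arm per wave.

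Using the recruited class size of about 11 would also overstate the effect, because up to 30% loss is planned for.

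**Conclusion.** The point holds in conditional form. The stated model does not match group delivery in two of the three arms, and its standard errors are too small to the extent that outcomes are correlated within class. The consequence is negligible to modest for each exercise arm against usual care at ICC 0.01-0.02, and material at 0.05-0.10. It is larger throughout for land against water. These figures rest on an assumed ICC, about 9 evaluable women per class, one class per exercise arm per wave, and a large-sample approximation that the simulation supports for the usual care comparison. Omitting wave is a minor loss of precision, not a source of false positives. The wording on numbers per wave is a clarity issue only.

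**What to change.** 1. Record a training-class identifier for every woman in the exercise arms.
2. Add wave as a factor in the between-group models.
3. Allow for class clustering in the two exercise arms only, with a partially nested mixed model and small-sample degrees of freedom such as Kenward-Roger. Do this at least as a sensitivity analysis for the primary FIQ comparison and for land against water.
4. Reword the wave sentence in the Interventions section to give the number per arm per wave, in agreement with 60/60/60.

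No extra patients, visits or procedures are needed. The cost is wider intervals and an imprecisely estimated class variance. For land against water, 5-6 classes per arm give about 2 × (5 − 1) = 8 to 2 × (6 − 1) = 10 degrees of freedom, and fitting wave as a fixed factor may use some of these. The critical value rises from about 1.99 to 2.31 (8 df) or 2.23 (10 df), which alone widens the interval by about 16% or 12%, before any increase in the standard error. This should be stated in advance.
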